## Abstract

**Background:**

Diuretic Resistance in Acute Heart Failure (DR-AHF) was designed to demonstrate the effectiveness of the early tolvaptan (a vasopressin-2 receptor antagonist) add-on therapy in patients with AHF with renal dysfunction and to provide clinical evidence of loop diuretic resistance.

**Methods and Results:**

This single-centered, open-labeled, randomized, and controlled trial enrolled 128 patients hospitalized with AHF, as participants. These patients with a wet-warm phenotype, whose estimated glomerular filtration rates are of ≥15 ml/min/1.73 m^2^ and ≤ 60 ml/min/1.73 m^2^, with a cumulative urine output of <300 ml 2 h after the first dose of intravenous furosemide, will be randomly assigned 1:1 to receive standard care with an uptitrating intravenous furosemide alone, or a combination therapy with 15 mg of tolvaptan administered once daily for 2 days. The standard furosemide treatment will follow the latest position statements of the Heart Failure Association. The primary endpoint is the cumulative urine output at 48 h. The key secondary endpoints include the improvement of fractional excretion of sodium at 6 h, the total dose of furosemide, and the incidence of worsening renal function (WRF) at 48 h.

**Conclusions:**

Although the combination of diuretic treatment has recently gained more attention due to its physiologically synergistic action, its advantages may be outweighed by the substantial risk of electrolyte disturbances and severe WRF. Further, there is no consensus on the time point for early starting of add-on therapy and for the preferred diuretic combination.

**Trial registration:**

NCT04331132.

## Introduction

Acute heart failure (AHF) represents a global burden, and more than 90% of patients with AHF experience congestion at admission, for which diuretics are the cornerstone therapy to achieve a euvolemic state (1). However, some complications, including renal dysfunction, urge us to increase the dose of diuretics to overcome diuretic resistance. High-dose loop diuretics may lead to serum electrolyte disturbances, especially hyponatremia, hypokalemia, arrhythmias, and more severe renal dysfunction (2). In the Diuretic Optimization Strategies Evaluation (DOSE) study, although the treatment with high-dose loop diuretics was not shown to be associated with adverse outcomes compared to a non-high-dose therapy, a more optimal decongestive therapy has not been developed despite the unacceptably high mortality rate (3). It is well known that the diuretic response is gradually self-limited after consecutive days of loop diuretic therapy (4). Therefore, timely modification of diuretic treatments according to the early signs of diuretic resistance, including the cumulative urine output within hours following intravenous loop diuretic administration, or combination therapy, was recommended to encourage decongestion (5).

Tolvaptan, a competitive vasopressin V2-receptor antagonist, is an oral diuretic that acts on the distal portion of the nephron. It inhibits the interaction between the antidiuretic hormone arginine vasopressin and the V2 receptor, thereby preventing the activation of the aquaporin channel systems and the consequent water reabsorption, leading to the net result of free water excretion (6). Evidence from clinical trials showed that tolvaptan, in combination with loop diuretics, is well tolerated in patients with congestive heart failure. It also ameliorates symptoms of congestion, increases sodium concentration in patients with hyponatremia, reduces loop diuretic dose, and lowers the risk of hypokalemia (7, 8). However, these findings are inconsistent among studies. Although both the EVEREST (Efficacy of Vasopressin Antagonism in heart failure) (9) and the AQUAMARINE (answering questions on tolvaptan's efficacy in patients with acute decompensated heart failure and renal failure) (10) trials confirmed the benefit of adding tolvaptan to a standard loop diuretic regimen for congestive heart failure symptoms using the Likert scale, TACTICS-HF (Targeting Acute Congestion with Tolvaptan in Congestive Heart Failure) (11) could not reaffirm these findings. Similar to decongestion efficacy, the combination of diuretic regimen including tolvaptan did not reduce the worsening renal function (WRF) rate in TACTICS-HF (11) and AQUAMARINE (10).

Moreover, it should be acknowledged that these studies did not focus on patients with diuretic resistance. Numerous studies have demonstrated that those who do not respond to intravenous loop diuretics are strongly associated with high mortality (12–14). Currently, there is no approved strategy for treating this high-risk subgroup.

Based on these considerations, diuretic resistance AHF (DR-AHF) was designed to determine whether the addition of tolvaptan to a modern diuretic strategy would result in a more optimal decongesting efficacy in AHF patients with diuretic resistance.

## Methods and Analysis

Diuretic resistance in acute heart failure DR-AHF is a single-centered, open-labeled, randomized, and controlled trial. This trial was approved by the independent ethics committee and the institutional review board at Nhan Dan Gia Dinh Hospital (registration: NCT04331132). The trial will be conducted per the principles of the Declaration of Helsinki and the International Conference on Harmonization (ICH) Good Clinical Practice guidelines. Written informed consent was obtained from participants before enrollment in the study.

### Study Population

To participate in DR-AHF, patients must be ≥20 years of age with wet-warm-phenotype AHF, whose estimated glomerular filtration rates (EGFRs) at admission are ≥15 and ≤ 60 ml/min/1.73 m^2^, and with a cumulative urine output of <300 ml, 2 h after the first dose of intravenous furosemide. The inclusion and exclusion criteria are listed in Table 1.

**Table 1 T1:** Inclusion and exclusion criteria for the diuretic resistance in acute heart failure (DR-AHF) trial.

**Inclusion criteria**
1. Aged 20–75 years 2. Admitted to hospital with a primary diagnosis of acute heart failure with wet-warm phenotype^*^ 3. Cumulative urine volume output <300 mL within 2 h after the first dose of intravenous furosemide 4. eGFR at admission 15–60 mL/min/1.73 m^2^
**Exclusion criteria**
1. Acute coronary syndrome 2. Anuria in the first 2 h after admission 3. Sepsis 4. Consciousness impairment 5. Pregnant or breastfeeding women 6. Severe valvular heart diseases (severe valvular stenosis or regurgitation) 7. Admission sodium level >140 mEq/L 8. Serum total bilirubin > 3mg/dL 9. Serum potassium >5.5 mmol/L 10. Allergy or contraindication to tolvaptan 11. Emergency indication for hemodialysis 12. Cardiogenic shock or mechanical circulation support

* *The wet-warm phenotype is defined as a patient with ≥2 clinical signs of congestion (bibasilar rales, bilateral ankle edema, ascites, jugular venous distension) and N-terminal pro B-type natriuretic peptide (NT-proBNP) at admission ≥900 pg/ml*.

### Study Flow and Loop Diuretic Strategy

On admission, patients with AHF with wet-warm phenotype will be given a starting dose of intravenous furosemide that is one to two times the 24-h oral furosemide dose prescribed before the admission home dose or 20–40 mg for treatment-naive patients with loop diuretic. Patients will be asked to immediately empty their urinary bladder before the first dose of intravenous furosemide. If eligible for inclusion in the study, at 2 h after the first intravenous furosemide, they will be randomly assigned 1:1 to receive a standard care with intravenous furosemide alone or a combination therapy with 15 mg of tolvaptan, once daily for 2 days. In both groups, the loop diuretic strategy strictly follows the modified 2019 position statement from the Heart Failure Association of the European Society of Cardiology (ESC) (5) (Figure 1). It is impossible to alter the dose of tolvaptan during the first 48 h of this study unless an adverse event was observed. After this period, the attending physicians decide whether to continue tolvaptan therapy. The standard treatments for heart failure, including the angiotensin-converting enzyme inhibitors, angiotensin II receptor blockers, vasodilators, beta-blockers, or digoxin, as well as the change from intravenous to oral loop diuretic or loop diuretic withdrawal, are left to the attending physicians 48 h after admission.

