### Measurements

Urine will be collected and monitored carefully at 6 h after randomization, and the cumulative urine output will be calculated every 24 h. Vital signs and symptom improvement assessed using a 7-point Likert scale will be recorded upon admission, and 24 and 48 h after randomization. Similarly, serum sodium, potassium, and chloride will be evaluated at admission and after 12, 24, and 48 h, respectively, while urinary creatinine and sodium will be sampled at randomization and after 6 h. After randomization, serum urea and creatinine will be re-assessed at 24 and 48 h. In addition, aspartate aminotransferase (AST), alanine aminotransferase (ALT), and N-terminal pro B-type natriuretic peptide (NT-proBNP) were evaluated upon admission and at the end of the study. A summary of the study assessment time frame is presented in Appendix 1. Senior cardiologists will perform echocardiography upon admission, and at 24 and 48 h afterward, according to the echocardiography protocol described in Appendix 2.

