### Endpoints

The primary endpoint was the cumulative urine output at 48 h after randomization. The secondary endpoints include the improvement of fractional excretion of sodium at 6 h, total dose of furosemide, changes in the body weight, net fluid loss, improvement of dyspnea by the 7-point Likert scale, reduction of diastolic dysfunction parameters on echocardiography, incidence of clinically relevant WRF, and changes of NT-proBNP at 48 h. Clinically relevant WRF is defined as an increase in serum creatinine level ≥0.3 mg/dl within 48 h accompanied by the doubling of furosemide dose according to the diuretic treatment protocol. A summary of the study endpoints is shown in Appendix 3.

Safety will be assessed based on the adverse effects reported throughout the study with vital signs, physical examination, clinical laboratory tests, and 12 lead-electrocardiogram. Safety topics of special interest include severe hypernatremia (plasma sodium increase > 12 mEq/24 h), hypokalemia, and hepatic injury (elevation of AST and/or ALT > three-fold the upper limit of the normal). Adverse effects and laboratory abnormalities were compared between the two treatment groups.

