### Statistical Consideration

#### Sample Size

In the REALITY-AHF dataset (*n* = 1682) (15), we identified and retrieved the records of the patients treated with an intravenous furosemide within 30 min of emergency department visits. Using the ESC Heart Failure Association definition (<150 ml urine output/h), we identified 95 patients with diuretic resistance in the first 90 min, while their urine output within 48 h was 3,896 ± 1,595 ml. Assuming that the add-on tolvaptan therapy could yield 1,000 ml more urine output at 48 h, we calculated the sample size of 128 patients with an enrollment ratio of 1:1 after adjusting for 15% dropout during the follow-up period. This sample size was intended to provide a 90% power and 0.05 type I error probability.

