Combination therapy offers many benefits in overcoming diuretic resistance. Most experts believe that it should not be initiated until the loop diuretic dose is up-titrated. However, no consensus has been reached regarding the time point for starting the add-on therapy. Although the combination diuretic treatment has recently gained more attention due to its physiologically synergistic action, its advantages may be outweighed by the substantial risk of electrolyte disturbances and a more severe WRF (2). Tolvaptan is promising for diuretic combination therapy. In the AQUAMARINE study (10), patients with AHF with renal dysfunction (defined as eGFR at admission 15–60 ml/min/1.73 m^2^) were randomized to tolvaptan add-on therapy or conventional diuretic treatment in the early stage of congestion (within 6 h after admission). This resulted in more diuresis and in better symptom relief without increasing the risk of WRF and electrolyte abnormalities. Recently, in a 3T trial (19), tolvaptan produced a higher cumulative urine output at 48 h and a lower risk of hyponatremia than the metolazone add-on therapy in patients with AHF and intravenous loop diuretics. The previous randomized trials and the current trial are summarized in Appendix 4. Overall, the DR-AHF trial is the first to evaluate the additive clinical value of treatment with tolvaptan in modern loop diuretic up-titrating therapy among patients with AHF and with verified diuretic resistance.

The DR-AHF trial has some limitations. First, as this is a single-center trial, some biases, such as selection bias, may not be entirely excluded. Moreover, this trial may be undersized to evaluate the prognostic impact of tolvaptan. Finally, this is an open-label trial in which the treatment of a doctor or the behavior of a patient can change.

In summary, the DR-AHF trial will demonstrate the efficacy of the timely intense loop diuretic monotherapy and tolvaptan combination treatment in the early stage of congestive heart failure with renal dysfunction and provide the clinical evidence of diuretic resistance.

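### Loop-diuretic discretion opens 48 h after admission, at least about 2 h before the primary urine-output window closes at 48 h after randomization

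*Protocol article*

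**What the plan says.** Three rules in the Protocol article set the timing.

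- **Start of treatment and randomization** (Study Flow and Loop Diuretic Strategy): "On admission, patients with AHF with wet-warm phenotype will be given a starting dose of intravenous furosemide"; then, if eligible, "at 2 h after the first intravenous furosemide, they will be randomly assigned 1:1".
- **End of the protocol-governed loop diuretic** (same section): the change from intravenous to oral loop diuretic "or loop diuretic withdrawal, are left to the attending physicians 48 h after admission".
- **Primary endpoint** (Endpoints): "The primary endpoint was the cumulative urine output at 48 h after randomization".

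The tolvaptan rule in the same section uses yet another phrase: "It is impossible to alter the dose of tolvaptan during the first 48 h of this study", adverse events excepted. The Measurements section uses both time points in one sentence, where vital signs and symptoms "will be recorded upon admission, and 24 and 48 h after randomization".

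**The concern.** The loop diuretic directly drives urine volume, which is the primary endpoint. If physicians may withdraw it or switch it to oral before the endpoint window closes, part of the primary measurement is taken under care that the protocol no longer controls.

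The permission is the same in both arms. But physicians know the allocation, and the Discussion accepts that "this is an open-label trial in which the treatment of a doctor or the behavior of a patient can change". A physician who sees a brisk response on tolvaptan, or a poor one on furosemide alone, could act differently by arm while urine is still being counted. The total furosemide dose, a secondary endpoint, would be exposed in the same way if it is counted to 48 h after randomization.

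The text only permits such a change. It does not say that any patient leaves the algorithm.

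**Working it through.** **1. Timing, counted from admission**

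- First intravenous furosemide: 0 h at the earliest (Study Flow and Loop Diuretic Strategy). Let *d* be any delay, *d* ≥ 0; the article gives no figure for it.
- Randomization: *d* + 2 h. It cannot properly come earlier, because urine output below 300 ml in the 2 h after that dose is an inclusion criterion (Table 1).
- Close of the primary window: *d* + 2 + 48 = *d* + 50 h.
- Start of physician discretion: 48 h.
- Gap: *g* = (*d* + 50) − 48 = *d* + 2 h, so at least 2 h.
- Share of the primary window at the minimum: 2/48 = 4.2%.

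This step needs no assumption about urine flow or variance.

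**2. The plan's sample size**

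Inputs (Sample Size): difference 1,000 ml, SD 1,595 ml, power 90%, type I error 0.05, dropout 15%, allocation 1:1. The test is two-sided (Statistical Methodology).

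- n per arm = 2 × (1.960 + 1.282)² × 1,595² / 1,000² = 53.5, rounded up to 54.
- With dropout: 54 / 0.85 = 63.5, rounded up to 64 per arm, or 128 in total.

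The stated 128 is reproduced.

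**3. What the gap could cost, as an illustration**

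The planning assumption is "Assuming that the add-on tolvaptan therapy could yield 1,000 ml more urine output at 48 h". Suppose that this difference accrues evenly over 48 h and that all of it is lost during the gap. The remaining difference is then 1,000 × (1 − *g*/48). With 54 evaluable patients per arm, SE = 1,595 × √(2/54) = 307 ml. Power = Φ(difference/SE − 1.960).

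| Gap *g* | Share of window | Difference lost | Difference left | Power (normal) | Power (t-test) |
|---|---|---|---|---|---|
| 0 h | 0% | 0 ml | 1,000 ml | 90.3% | 89.8% |
| 2 h (minimum) | 4.2% | 42 ml (0.03 SD) | 958 ml | 87.7% | 87.2% |
| 4 h (assumed) | 8.3% | 83 ml (0.05 SD) | 917 ml | 84.8% | 84.1% |
| 6 h (assumed) | 12.5% | 125 ml (0.08 SD) | 875 ml | 81.3% | 80.6% |

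The 4 h and 6 h rows assume delays of 2 h and 4 h from admission to first dose. All rows are scenarios, not bounds. They show losses only, although arm-dependent care could also widen the observed difference.

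**The case against.** The strongest reply is that this is loose wording. The article is casual about its clocks. The tolvaptan rule runs over the first 48 h of the study, the 24 h evaluation in the Figure 1 legend has no anchor, and electrolytes and echocardiography are timed from admission while vital signs are timed from randomization. In the Measurements sentence quoted above, admission is only a baseline visit and not the start of a 48 h clock. The loop diuretic is also said to follow the cited position statement strictly in both arms, and Figure 1 and Appendix 1, which might give an end time, are not visible here.

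Much of this is fair, and it limits confidence that the authors meant to run two clocks. It does not remove the point. The statement about strict adherence gives no end time, and the only stated handover of the loop diuretic is tied to admission. If randomization was meant, the text needs the same correction.

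The second reply concerns size, and it largely stands. Losing the whole treatment difference in the gap is extreme: the discretion covers the background diuretic, applies to both arms, and leaves the tolvaptan dose alone. If only a quarter of the 2 h difference were lost (an assumption), about 10 ml would go and power would be about 89.7%. The article gives furosemide on admission, so it offers no support for the 4 h and 6 h gaps; they show sensitivity and nothing more.

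**Conclusion.** The concern holds as a minor point. Followed as written, the protocol opens unblinded discretion over the loop diuretic at least about 2 h before the primary endpoint is complete, which is 4.2% of the window at the minimum. That rests only on the stated times.

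The consequence is less certain. The expected effect on urine output is small and its direction is unknown. The fall in power from about 90% to about 88% at 2 h depends on even accrual and on complete loss of the difference in the gap. The sample size reproduces, and the randomized comparison is not affected. Confidence is medium, because the reference to admission may be a slip for randomization.

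**What to change.** In Study Flow and Loop Diuretic Strategy, tie the start of physician discretion over the loop diuretic to 48 h after randomization instead of 48 h after admission. The protocol-governed loop-diuretic period then covers the whole primary window and the gap is zero.

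The cost is one wording change, with no added visits, assessments or patients; the total stays at 128. Patients remain on the protocol-governed loop diuretic about 2 h longer, or more if the first dose was delayed. The rule in the Figure 1 legend that ends the study protocol at 24 h for symptomatic hypovolemia is kept.

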**Figure 1 F1:**
[figure not shown]
Study protocol. At 24 h, study participants will be evaluated by the same investigator ([name], [name], [name], [name], or [name] ). If the investigator determines that the patient is absolutely hypovolemic and symptomatic, the study protocol will be ended.

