#### Randomization

The study is an open-label randomized trial, and randomization will be performed *via* a web portal constructed by a third party (www.randomization.com).

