#### Statistical Methodology

The intention-to-treat the population, which included all randomized patients to whom at least one dose of tolvaptan was administered, will be analyzed for the primary and secondary endpoints. As an exploratory analysis, we will evaluate interactions between tolvaptan add-on treatment and pre-specified subgroups on primary and secondary outcomes. Subgroups were defined for age (age > 65 and ≤ 65), eGFR at admission (eGFR 15–29 and eGFR 30–60), sodium and chloride levels at admission (above or below median), furosemide-naive or not, diuretic response achieved in the first 2 h after initial intravenous injection, blood urea nitrogen/creatinine (above or below median), and left ventricular ejection fraction ≤ 40 or >40%. A *P*-value of < 0.05 was considered statistically significant. Continuous variables are expressed as mean ± standard deviation if normally distributed or as median (interquartile range) if otherwise. When necessary, the variables were transformed for further analysis. Statistical significance was defined as two-sided 5%, and all analyses were performed using IBM SPSS^®^ (version 24.0) and R version 3.5.2 (R Foundation for Statistical Computing, Vienna, Austria; ISBN 3-900051-07-0, URL http://www.R-project.org). Normality was assessed using the Shapiro-Wilk test. The independent Student's *t*-test or Mann-Whitney U test was used to compare the two treatment groups according to each parameter. Categorical data will be displayed as a percentage or number and compared using Fisher's exact test. The relationship between baseline characteristics and outcomes will be compared by one-way analysis of variance, Kruskal-Wallis test, or χ^2^ test, as appropriate.

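### The 24 h rule in the Figure 1 legend ends the study protocol, not just study treatment; read literally, it drops the second day of the primary endpoint in patients selected on a consequence of diuresis

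*Protocol article*

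**What the plan says.** The legend to Figure 1 of the protocol article places an evaluation by the investigator at 24 h and states: "If the investigator determines that the patient is absolutely hypovolemic and symptomatic, the study protocol will be ended".

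The other passages that bear on this rule are:

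- **Endpoints:** "The primary endpoint was the cumulative urine output at 48 h after randomization". Several secondary endpoints are also taken at 48 h.
- **Measurements:** "the cumulative urine output will be calculated every 24 h", with symptom, laboratory and echocardiographic assessments at 24 and 48 h. No exception is stated for a patient whose protocol was ended.
- **Study Flow and Loop Diuretic Strategy:** for furosemide: "loop diuretic strategy strictly follows the modified 2019 position statement from the Heart Failure Association of the European Society of Cardiology (ESC) (5) (Figure 1"). For the add-on drug: "It is impossible to alter the dose of tolvaptan during the first 48 h of this study unless an adverse event was observed".
- **Randomization:** "The study is an open-label randomized trial".
- **Statistical Methodology:** the set called intention-to-treat "will be analyzed for the primary and secondary endpoints".

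**The concern.** The sentence in the legend is a conduct rule, and what it ends is the protocol as a whole. Where the article means treatment it can say so: Study Flow speaks of the tolvaptan dose and of withdrawing the loop diuretic. The 48 h schedule under Measurements does not settle the matter, because that schedule is part of the protocol being ended.

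A site that followed the words as written could stop charting urine at 24 h. The loss would not be random. Hypovolemia is plausibly a result of brisk diuresis, which is what the trial measures, and the person judging it knows the treatment. Under the trial's own hypothesis of more urine on tolvaptan, such stops would be expected more often in that arm. The 15% dropout allowance protects the number of patients analysed but does nothing about selective loss. A statistical analysis plan can say how to handle a missing 48 h volume, but it cannot recover urine that nobody collected.

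**Working it through.** **1. The plan's own figure.** Sample Size gives SD 1,595 ml, a 15% dropout allowance, 90% power and type I error 0.05, with the effect set by "Assuming that the add-on tolvaptan therapy could yield 1,000 ml more urine output at 48 h". Statistical Methodology makes the test two-sided.

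n per arm = 2 × (1.960 + 1.282)² × (1,595/1,000)² = 53.5, so 54 per arm and 108 in all. 108/0.85 = 127.1, which rounds up to 128 in two equal arms. The stated total of 128 is reproduced and is not in dispute.

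**2. The two readings.**

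| | Treatment-only | Literal |
|---|---|---|
| What ends at 24 h | tolvaptan and the furosemide algorithm | the whole protocol |
| 24–48 h urine | collected | not collected |
| 48 h assessments | done | not done |
| Primary comparison | complete | incomplete in patients selected on diuresis |

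The text shown does not decide between them.

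**3. Size under the literal reading (illustrative).** The documents give no stop rate, no split of urine by day and no link between the judgement and volume. All of these are assumptions:

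- Day-1 and day-2 volumes are bivariate normal with equal means by day (1,948 ml per day on control, 2,448 ml on tolvaptan, from 3,896 and 4,896 over 48 h). Their correlation ρ is 0.5, so the daily SD is 1,595/√3 = 921 ml.
- A patient is stopped when a judgement score exceeds a cut that is the same in both arms. The score correlates k with day-1 volume.
- With control stop rate p: c₀ = z(1 − p) and c₁ = c₀ − k × 500/921.
- Completer difference = 1,000 − k × √((1 + ρ)/2) × 1,595 × [L(c₁) − L(c₀)], where L(c) = φ(c)/Φ(c).
- Power comes from a non-central t with the truncated SDs. Stops count within the 15% allowance, so n = 64 × 0.85 = 54.4 per arm throughout. With no stops this gives 90.0%.

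Worked case, k = 0.7 and p = 5%: c₀ = 1.645; c₁ = 1.645 − 0.380 = 1.265, which is 10.3% stops on tolvaptan. L(c₁) − L(c₀) = 0.1999 − 0.1086 = 0.0913. The difference is 1,000 − 0.7 × 0.866 × 1,595 × 0.0913 = 912 ml, with power 87.2%.

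| Link k | Control stops | Tolvaptan stops | Completer difference (ml) | Power |
|---|---|---|---|---|
| 0.5 | 1 / 2 / 5% | 2.0 / 3.7 / 8.5% | 985 / 976 / 958 | 89.5 / 89.3 / 88.7% |
| 0.7 | 1 / 2 / 5% | 2.6 / 4.7 / 10.3% | 966 / 948 / 912 | 89.0 / 88.4 / 87.2% |
| 1 (sharp cut, extreme) | 1 / 2 / 5% | 3.7 / 6.5 / 13.5% | 920 / 880 / 803 | 87.6 / 86.1 / 82.8% |

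In patient numbers, one control stop in 64 goes with about 2 to 3 tolvaptan stops in 64. The difference is then 979 / 955 / 896 ml and power about 89 / 89 / 87% for the three links. Changing ρ to 0.3 or 0.7 moves the worked case to 925 or about 899 ml. If nobody is stopped, or stops are equally selective in both arms, there is no bias.

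**4. The same patients with collection continued.** Assume that stopping diuretics halves day-2 output. By simulation, at 5% control stops, the as-randomized difference is about 939 / 910 / 857 ml for links 0.5 / 0.7 / 1, with power about 88% in each case.

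**The case against.** The case for a harmless meaning is strong. The legend's own title for the figure is the study protocol, and Study Flow cites that figure for the diuretic strategy, so ending it may simply mean leaving the scheme drawn there. Study Flow makes the furosemide strategy strict, leaves loop diuretic withdrawal to physicians only from 48 h after admission, and bars tolvaptan changes without an adverse event. A 24 h release for a volume-depleted patient with symptoms fills an evident safety gap. Endpoints also uses the word protocol for the diuretic treatment algorithm. No passage says that urine collection stops. Neither the figure's drawing nor the appendix with the assessment schedule is at hand, and an article may leave follow-up of stopped patients to the full protocol.

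Most of this stands, and it rules out the stronger reading a reader might infer, that the plan definitely discards the second-day urine. The documents do not establish that. It does not dispose of the point, which rests on a sentence the article states and not on a missing one. That sentence is broader than treatment, and following it as written would lose data irrecoverably.

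It is also fair that the numbers are small and that the fix recovers little power. At 5% control stops, power is 88.7 / 87.2% among completers and about 88% with collection continued, for links 0.5 and 0.7. The difference in ml is no closer to 1,000 either (958 / 912 against 939 / 910). Only the sharp-cut extreme shows a visible gain.

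**Conclusion.** The point holds as a minor one. The legend's rule is worded more broadly than treatment and acts halfway through the primary endpoint window. It depends on an open-label judgement of a state that follows from diuresis. If applied literally, it leaves the as-randomized comparison of 48 h urine output incomplete in a response-dependent way. The reason to act is to keep that comparison complete, not to recover power.

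With assumed control stop rates of 1 to 5% and a weak or moderate link, the completer difference would be 912 to 985 ml against a true 1,000 ml, with power 87.2 to 89.5%. The extreme link with 5% control stops gives 803 ml and 82.8%. Patients enter congested and with a poor 2 h response, so stops may be rare and the effect close to nil.

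Two further inferences are not supported. The first is a false positive: if stops are more frequent on tolvaptan, the loss pulls the difference toward zero. The second is a heavy loss of power from counting a stopped patient's 24 h volume as the 48 h total. With day 2 assumed to be 40–50% of the total and 54 per arm, 15% stops on tolvaptan against 5% on control would give 730–784 ml and 66–72% power. No passage says that stopped patients would be analysed that way.

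**What to change.** Reword the sentence so that, at 24 h, a patient judged volume-depleted with symptoms stops study treatment only, meaning tolvaptan and the furosemide algorithm. The clinical decision stays with the investigator. Add that urine collection and all scheduled assessments continue to 48 h after randomization, that these patients are analysed as randomized with their observed 48 h volume, and that stops are reported by arm.

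The cost is that rewording and one more day of inpatient urine charting in a few patients. If treatment-only was the intended meaning, the change merely confirms it. The one real trade-off is that the estimate then includes the effect of stopping diuretics, and so describes the strategy as delivered. That is consistent with an intention-to-treat comparison.
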